### Aims and objectives

In analogy to the original research design, we will assess self-reported perceived stress and reactivity to stress and symptoms of anxiety and depression as the main outcome variables. To complement the subjective measures, physiological markers of stress (resting blood pressure, indicators of heart rate variability, hair cortisol levels and salivary alpha-amylase) will be measured in the leaders. Assuming that leadership behaviour and leaders’ individual stress levels impact the work stress of their employees, we will assess the effects of the intervention on the leaders’ employees as well. Therefore, employees will rate their own perceived work stress and the leadership behaviour of their superior on questionnaires before and after the stress intervention. Furthermore, the intervention will be evaluated in the light of its economic and organizational benefits: secondary evaluation criteria will therefore be number of sick days, physiological health, and absenteeism, the relationship between leaders and employees as assessed by leaders and employees, and their perception of working conditions.

The study is designed as a randomized controlled trial with a waiting control group evaluating the effectiveness of a stress management training at 6 and 12-months-follow-up measurement time points.

In short, the main objectives of KMU-GO are:
To investigate the effectiveness of a stress management training for leaders based on their subjectively perceived mental health and objective physiological markers of stress as well as other outcome variables such as anxiety and depressive or psychosomatic symptoms or sick days in comparison with a waiting control group.To investigate indirect effects on the subjectively perceived mental health of the employees of the trained leaders as well as on their emotional and cognitive irritation, well-being, perception of working conditions and the quality of leader-employee relationship.To evaluate the cost-utility of the stress management training from a societal perspective.To replicate the effects of the previous MAN-GO [48] study, thereby expanding the results to all genders, the SME sector and all industries.To additionally evaluate the cost-effectiveness of the stress management training at the company and societal level

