## Method

### Population and sample size

#### Leaders

The target group are leaders of small and medium-sized enterprises (SMEs). We define SMEs as enterprises with up to 500 employees [50, 51] without regarding the annual sales. Leaders of all genders aged between 18 and 65 years are allowed to participate as long as they are not about to retire within the next year. A sample size of *n* = 100 participants in the intervention group and *n* = 100 participants in the waiting control group is planned (*N* = 200 participants).

The sample size calculation was performed using G*Power3.1. Based on a 2 × 3-mixed design (factor 1 (group): intervention or waiting control group; factor 2 (point in time): baseline, 6 months and 12 months later) the required sample size for a MANOVA with measurement repetition was estimated using the following predefined parameters: mean effect size f = .25 (Ω = 0.06), α-error = .05, test strength 1-β = .80. This results in a required sample size of *n* = 158 participants (*n* = 59 per group). The calculation of the required sample size was based on the procedure proposed by Prajapati et al. (2010) to calculate the required sample sizes for all possible effects (within, between, interaction) of the present design and to use the largest calculated sample size. Due to the high effort of the outcome criteria to be collected (e.g., saliva samples, 24-h heart rate variability) a high lost-to-follow-up as well as numerous missing values can be expected. We therefore calculate with a total failure rate of 21% (lost-to-follow-up and due to missing values), resulting in a required sample size of *N* = 200 (*n* = 100 per group at T_0_).

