#### Statistical methods

Data will be analysed using the statistic software IBM SPSS Statistics 27. Descriptive analyses will be conducted after the baseline. A multivariate analysis of variance (MANOVA) with all relevant outcome parameters as specified above will be calculated in order to test the effects of the intervention on different dependent variables. Potential covariates will be included in the analysis. Therefore, if relevant covariates occur, a MANCOVA will be performed instead of the MANOVA. A covariate will be identified as such, if a demographic variable will correlate with the outcome variable or if there is a significant difference between the intervention group and the waitlist control group across this variable.

To evaluate the effects of the stress management intervention more specifically, changes in outcome variables will be analysed by two-factorial ANOVA with repeated measures and group (intervention vs. waiting control group) as a between-person effect. The core hypothesis is that perceived stress and physiological stress parameters of leaders will significantly decrease from baseline to follow-up measurements for participants in the intervention group. Thus, we will test the interaction effect of time x group for the different outcome variables. Where necessary, Bonferroni correction will be applied to avoid inflation of the type one error by multiple comparisons.

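### The Bonferroni correction is valid, but Holm's step-down version controls the same error rate and would be somewhat more powerful if several outcomes respond

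*Protocol article*

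**What the plan says.** All references are to the protocol article.

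- **Statistical methods.** After a MANOVA (or MANCOVA), each outcome is analysed by a two-factor repeated-measures ANOVA: "Thus, we will test the interaction effect of time x group for the different outcome variables". The next sentence is the whole multiplicity rule. It says that, where needed, "Bonferroni correction will be applied to avoid inflation of the type one error by multiple comparisons". The rule is conditional. It gives no number of tests, no family and no step-down version, and no simultaneous confidence intervals are planned for these tests.
- **Statistical methods, core hypothesis.** Several outcomes are expected to move together: "perceived stress and physiological stress parameters of leaders will significantly decrease from baseline to follow-up measurements for participants in the intervention group".
- **Aims and objectives.** The study will assess "self-reported perceived stress and reactivity to stress and symptoms of anxiety and depression as the main outcome variables".
- **Population and sample size, Leaders.** The calculation uses "mean effect size f = .25 (Ω = 0.06), α-error = .05, test strength 1-β = .80" and leads to 158 analysed and 200 randomised. The alpha carries no adjustment for multiple outcomes.

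**The concern.** Plain Bonferroni compares every p-value in a family of m tests with .05/m. Holm orders the p-values and compares the smallest with .05/m, the next with .05/(m-1), and so on up to .05, stopping at the first failure. It needs no assumption beyond Bonferroni's, and its set of rejections always contains Bonferroni's. For the tests themselves, then, naming Bonferroni is the less efficient of two equally valid choices.

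The difference appears only when two or more outcomes truly respond, which is what the core hypothesis expects. In that case some real effects on single outcomes could miss the Bonferroni limit although the same data would support them at the same family-wise error rate. The sample size was set at an unadjusted alpha, so any correction across outcomes draws on power that was not budgeted for it.

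**Working it through.** **1. Reproduce the article's sample size.** Inputs from the Leaders section: 2 groups, 3 time points, f = .25, alpha = .05, power .80, 21% loss. For the within-between interaction in a repeated-measures MANOVA:

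- lambda = N x f² = 158 x 0.0625 = 9.875
- df1 = (2-1)(3-1) = 2; df2 = 158 - 3 = 155
- Power from the noncentral F: 0.802 at N = 158 and 0.799 at N = 157
- 158 / 0.79 = 200

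The figures 158 and 200 reproduce. The printed 59 per group does not fit them (158 / 2 = 79). That is a separate matter, and 158 is used here.

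**2. Power of one test at the Bonferroni limit, N = 158.** Same formula with alpha = .05/m. The number of tests m is an assumption:

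| m | alpha | power |
|---|---|---|
| 2 | .025 | 0.714 |
| 4 | .0125 | 0.620 |
| 5 | .01 | 0.590 |
| 8 | .00625 | 0.527 |
| 12 | .00417 | 0.474 |

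**3. Bonferroni against Holm, four outcomes.** Four is the count if perceived stress, stress reactivity, anxiety and depression are taken separately. The Holm limits are then .05/4 = .0125, .05/3 = .0167, .05/2 = .025 and .05. Two simulations were run, with the correlation between outcomes assumed:

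- *A*: Hotelling T² per outcome, 79 per arm, squared Mahalanobis distance 0.25, so lambda = (79 x 79 / 158) x 0.25 = 9.875; 6,000 trials per setting.
- *B*: 2-df chi-square statistics with the same lambda; 100,000 replicates. It ignores the finite denominator df, so it runs slightly high (0.637 against the exact 0.620).

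| Outcomes responding (f = .25) | Simulation, correlation | Mean power per responding outcome, Bonferroni | Holm |
|---|---|---|---|
| 4 of 4 | A, 0 / 0.3 / 0.6 | 0.622 / 0.621 / 0.626 | 0.733 / 0.717 / 0.712 |
| 4 of 4 | B, 0 / 0.5 | 0.637 / 0.637 | 0.744 / 0.726 |
| 2 of 4 | A, 0.3 | 0.620 | 0.643 |
| 2 of 4 | B, 0 / 0.5 | 0.637 / 0.637 | 0.662 / 0.659 |
| 1 of 4 | B, 0 / 0.5 | 0.638 / 0.632 | 0.639 / 0.633 |

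If all four respond, the chance of showing all four rises from 0.152 / 0.245 / 0.358 to 0.398 / 0.464 / 0.562 (A), and from 0.164 / 0.329 to 0.407 / 0.541 (B).

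The chance of at least one significant result is the same, because Holm's first step is the Bonferroni test. With all four responding, B gives 0.982 for both methods at correlation 0 and 0.899 for both at 0.5.

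**4. Other family sizes (B, correlation 0.5, all outcomes responding).** Mean power goes from 0.726 to 0.778 for m = 2, from 0.546 to 0.654 for m = 8, and from 0.494 to 0.603 for m = 12.

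**5. Error rate.** With four outcomes and no effect anywhere, the family-wise error is 0.051 for both methods in A, and 0.049 and 0.043 for both in B. With two true effects (A), the error among the two null outcomes rises from 0.026 to 0.041, still below .05. In B, Holm rejected every hypothesis that Bonferroni rejected, in every replicate.

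**The case against.** **The premise is partly inferred.** The sentence is conditional and speaks of multiple comparisons without saying which. It may refer to comparisons between time points within an outcome as well as, or instead of, the set of outcomes. A reader might infer that each of a known number of outcome tests is held to .05/k, but the article states no such k. This stands, and it means the gain can only be given under assumptions. It does not affect the ranking: Holm rejects at least as much as Bonferroni in any family.

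**Nothing is stated wrongly.** Bonferroni is valid, and the details may be set out in an analysis plan that is not shown. That also stands. The unstated family is therefore not counted as a fault here. The correction method is named in the article, though, and can be improved where it is named.

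**The MANOVA comes first.** If it acts as a gate, power changes under both methods, and the simulations leave it out. The gate would apply equally to both, so Holm would still lose no rejection, but the size of the gain could differ.

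**The larger gains are the favourable case.** They need every outcome to have f = .25, which the article gives only as a sample-size input. This stands.

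**The power is not lost for nothing.** A reader might infer that Bonferroni has no advantage at all. It does provide simple simultaneous confidence intervals, which Holm does not match. The article plans no such intervals for these tests, so the advantage goes unused but is real.

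**Conclusion.** The point holds as a cheap improvement in efficiency. Bonferroni protects the type I error, and the article does not support reading this as an error-control fault.

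At 158 analysed and f = .25, with an assumed four outcomes and correlations of 0 to 0.6, Holm raises mean power per outcome by about 9 to 11 points if all four respond. The gain is about 2 points if two respond and about 0.1 point if one does. The chance of at least one significant result is essentially unchanged.

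Holm does not restore 80% power per outcome: 0.71-0.74 is still below it, because the sample size used an unadjusted alpha. Which tests form the family, and that unadjusted alpha, matter more for the trial than the choice between these two procedures.

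**What to change.** Keep the sentence in Statistical methods with its condition and its general scope, so that no other comparison loses its correction. Change only the method named, from Bonferroni to the Bonferroni-Holm step-down procedure with family-wise alpha .05. Then add:

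> For the outcome-wise time x group tests, the family is the set of main outcome variables named under Aims and objectives.

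No sidedness should be attached, because the interaction is a 2-df F test. The sponsor should list the family by scale, since the Data collection section assigns perceived stress to the stress-reactivity questionnaire, so the count may be three rather than four. If the physiological parameters in the core hypothesis are meant to belong to the family, they should be added by name.

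**Cost.** About two lines of text, settled before outcome data are seen. Holm needs only the same p-values put in order, with no extra participants, data or assumptions. The small downside concerns intervals: any reported beside Holm-adjusted p-values should be labelled as unadjusted, since they can exclude zero where the adjusted test does not reject, or Bonferroni intervals can be given as a supplement.

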#### Health economic evaluation

Incremental cost-effectiveness analyses (ICEA) by means of the net-benefit approach [76, 77] will be performed from the perspective of SME companies and from the societal perspective. For the SME perspective the incremental costs of the intervention compared to non-intervention incurred by the companies will be related to the incremental reduction in sick-leave days. For the societal perspective the incremental total costs of illness including the direct costs of health care resources and the indirect costs due to productivity losses will be related to the incremental gain in quality adjusted life years (QALYs) [76, 77].

Point estimates of incremental costs effectiveness ratios (ICER) will be computed for both perspectives. Stochastic uncertainty of the ICER will be estimated by means of non-parametric bootstrapping with 4000 replications [76, 78]. ICER will be interpreted on the basis of the cost-effectiveness plane [76]. The significance of the ICER will be estimated on the basis of the cost-effectiveness acceptability curve [76].

Results of the ICEA from the company perspective will provide the necessary maximum willingness to pay for the prevention of one sick leave day at which the intervention is cost-effective at the company level with a probability of 95%. Results of the ICEA from the societal perspective will provide the necessary maximum willingness to pay for the gain of one additional life year in full health (QALY) at which the intervention is cost-effective at the level of the German national economy with a probability of 95% [76].

### Handling of missing and spurious data and drop outs

We do not expect item-wise missing values as all questionnaires will be assembled digitally with notifications if items are missing. However, in the case of missing items for questionnaires the missing item score will be substituted by the mean item score of the remaining questionnaire items.

As participating leaders can withdraw from the physiological assessments, we expect some missing data for the physiological stress measures. In physiological stress assessments, measurement errors may occur. Especially for heart rate variability, which will be measured over a period of 24 h without surveillance of clinical personnel, measurement errors may occur. Thus, all data will be checked for plausibility and carefully tested against potential measurement errors. Participants with missing or spurious data will remain in the sample and will only be excluded for those analyses that involve the missing data.

As the study has a longitudinal design that extends over 1 year in time, some dropouts will be inevitable. We will, however, endeavour to retain as many participants of the original sample and will try to maximize compliance with the study’s data assessments. We accounted for some dropouts in our power analyses. Participants who drop out after t1 (the first follow-up measurement) will be included in the data analyses up to this point in time. An intention-to-treat analysis will be conducted to evaluate whether the sub-sample of dropouts significantly differs from the adherent sample.

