#### Leaders

Leaders are going to be asked to complete single items, 9 questionnaires and three physiological measures.

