##### Questionnaires

All subsequent questionnaires are collected at three measurement times (T_0_, T_1_, T_2_). The target outcome is the change in the intervention group compared to the waiting control group over time.

*Perceived Stress-Reactivity-Scale* [52]. The PSRS assesses perceived stress reactivity on 5 scales: reactivity to social assessment (5 items, “If I am wrongly criticized by others ...”), reactivity to failure (4 items, e.g., “If I did something wrong ...”), reactivity to social conflict (5 items, e.g., “When I argued with other people ...“), reactivity to work overload (5 items, e.g., “When I have little time for my work ...”) and prolonged reactivity (4 items, e.g., “When I have free time after strenuous work ...“). In addition, an overall score can also be calculated. All items are answered by agreeing with one of three default answers. Scale reliability is sufficiently high and varies between α = .79 and α = .82 with α = .89 for the total score (Cronbach’s Alpha).

*Effort Reward Imbalance Questionnaire (ERI,* [53]). The ERI conducts self-assessments of psychosocial workloads on three scales: exertion (6 items, e.g., “I am often interrupted and disturbed in my work”), reward (11 items, e.g., “I get the recognition I deserve from my superiors”) and over-commitment (6 items, e.g., “Those who are closest to me say I sacrifice myself too much for my job”). Reward is a multidimensional concept and consists of the following subscales: recognition, pay/progression and job security. The exertion and reward dimensions are assessed with five-point Likert-scale, ranging from “unexposed to adverse condition” (1) to “exposed to adverse conditions and very distressed” (5). Over-commitment is measured with a four-point Likert-scale, ranging from “Strongly disagree” (1) to “Strongly agree” (4). The internal consistency of the scales is sufficiently high and between α = .62 and α = .90 (Cronbach’s Alpha).

*Hospital Anxiety and Depression Scale (HADS, Herrmann, 1997).* The HADS is a 14-item questionnaire (7 items each for anxiety and depression) for self-assessment of depressive (e.g., “I still enjoy the things I used to enjoy”) and anxiety symptoms (e.g., “Worrying thoughts go through my mind”). All items are answered by agreeing with one of four default answers. Scale reliability is high with α = .86 for anxiety and α = .91 for depression (Cronbach’s Alpha).

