*Leader-Member Exchange 7 (LMX-7, Graen & Uhl-Blen, 1995).* The LMX-7 questionnaire consists of 7 items assessing the relationship between leaders and employees (e.g., “How well do you understand the work-related problems and needs of your employees?”) on a 5-point Likert-Scale. Cronbach’s Alpha is high: α = .84 [54].

*Occupational Self-Efficacy Expectations – short scale (*Berufliche Selbstwirksamkeits-erwartung, BSWE*, Schyns & von Collani, 2014).* The BSWE *–* short scale consists of 8 items measuring occupational self-efficacy expectations (e.g., “When unexpected situations arise at work, I always know how to act”) with a 6-point Likert-Scale ranging from “completely true” (1) to “not true at all” (6). Scale reliability is high with α = .84 (Cronbach’s Alpha).

*Psychosocial Safety Climate Questionnaire 4 (PSC-4,* [55]). The PSC-4 is a short questionnaire with only 4 items measuring the Psychosocial Safety Climate at work (e.g., “Senior management show support for stress prevention through involvement and commitment”). All items are answered using a 5-point Likert-Scale, ranging from “strongly disagree” (1) to “strongly agree” (5).

*Operationalized psychodynamic diagnosis structure questionnaire (OPD-SF, Ehrental* et al.*, 2012).* The OPD-SF assesses the Axis 4 (Structure) from the Operationalized Psychodynamic Diagnostic system (OPD). Only two of the five dimensions are used for the purpose of this study: self-awareness (12 items, e.g., “I often have feelings that I cannot understand”) and self-regulation (13 items, e.g., “When I’m very upset, I often act rashly”). Items are measured on a five-point Likert-scale ranging from “strongly disagree” (1) to “strongly agree” (5). Cronbachs α ranges from .88 to 91 (self-awareness) and .82 to .84 (self-regulation) [56].

*Client Sociodemographic and Service Receipt Inventory (CSSRI,* [57]). The use and costs of health care resources will be estimated by means of the CSSRI adapted for the application in the target population [57].

*EuroQol’s questionnaire for health related quality of life (EQ-5D 5 L,*[58]*).* Health-related quality of life will be assessed by means of the EuroQol EQ-5D 5 L. The EQ-5D 5 L defines subjective health states at the following five dimensions Mobility, Self-care, Usual activities, Pain and discomfort, Anxiety and depression at a five-level scale [58]. The individual health states will be evaluated by means of country-specific representative preference based value sets [59].

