##### Questionnaires

*Short questionnaire for work analysis* (ger.: Kurzfragebogen zur Arbeitsanalyse, KFZA, [68]). Working conditions will be assessed by the KFZA, which consists of eleven scales derived from 26 items. These scales comprise Decision latitude, Variety of work, Task identity, Social support, Teamwork, Workload (qualitative), Workload (quantitative), Interruption of work, Environmental stress, Information and codetermination, Company benefits. Sample items are: “How much influence do you have on what work is assigned to you?” and “I am often under time pressure”. All items are measured on a 5-point Likert scale ranging from 1 “does not apply at all” to 5 “is completely true”. The internal consistency of the scales is set between .40 and .76 (Cronbach’s α); in studies with larger samples Cronbach’s α ranged from .63 to .80 [69].

*Cognitive and emotional irritation scale* (IS [70]). The IS measures perceived cognitive and emotional strain. Irritation refers to a psychological state of impairment due to the experience of goal-discrepancy. The IS consist of 8 items that have to be answered on a 7-point Likert scale resulting in two first-order factors: First, Rumination (e.g., “Even when I am on vacation, I sometimes have to think about problems at work”) invokes increased efforts in order to achieve goals, whereas the second factor Irritability (e.g., “I get angry easily”) reflects a tendency to lose the incentive to pursue a certain goal. Internal consistency scores range from .85 to .97 for both subscales.

*Subjective psychological well-being* (WHO-5, Bech et al., 2003). Employees’ well-being will be measured using the five-item World Health Organization Well-Being Index (WHO-5) representing the most widely used questionnaire for measuring this construct [71]. Items are assessed on a 6-point Likert scale, ranging from 0 “at no time” to 5 “all of the time” concerning the last 2 weeks (e.g., “… I have felt calm and relaxed”). The raw score is multiplied by 4 resulting in a final score ranging from 0 to 100 (representing the best possible well-being). The WHO-5 is suitable for depression screening. The split-half reliability (Guttman’s coefficient) is r_tt_ = .87 (Brähler et al., 2007).

*Effort Reward Imbalance* (ERI, [53]) and *Relationship between employees and their managers* (LMX-7, Schyns & Paul, 2014). Both questionnaires are already described in section 2.3.1.

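### The missing-item rule averages over the whole questionnaire, which is wrong for instruments scored by subscale and does not suit EQ-5D 5L or CSSRI; the effect is probably small

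*Protocol article*

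**What the plan says.** The rule is in the protocol article under Handling of missing and spurious data and drop outs. The authors begin with "We do not expect item-wise missing values as all questionnaires will be assembled digitally with notifications if items are missing". For the case that an item is missing after all, "the missing item score will be substituted by the mean item score of the remaining questionnaire items". The rule names no subscale and exempts no instrument.

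The descriptions under Outcome variables show what the rule would act on:

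- **PSRS** (leaders): "The PSRS assesses perceived stress reactivity on 5 scales", of 5, 4, 5, 5 and 4 items, with an overall score also possible.
- **ERI** (leaders and employees): exertion 6 items, reward 11, over-commitment 6. Exertion and reward are scored 1 to 5, but "Over-commitment is measured with a four-point Likert-scale" (1 to 4).
- **HADS** (leaders): 7 anxiety and 7 depression items.
- **OPD-SF** (leaders): two dimensions are used, of 12 and 13 items.
- **KFZA** (employees): "which consists of eleven scales derived from 26 items".
- **EQ-5D 5L** (leaders): five dimensions with five levels each. "The individual health states will be evaluated by means of country-specific representative preference based value sets".
- **CSSRI** (leaders): use and costs of health care resources.

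On the count of instruments, the protocol says: "Leaders are going to be asked to complete single items, 9 questionnaires and three physiological measures".

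**The concern.** A person-mean fill-in is defensible when the remaining items measure the same thing on the same response format. Here the mean runs over everything under one questionnaire title. For an instrument with separate subscales, the value filled in comes largely or mostly from items of other constructs. In KFZA these include resources such as decision latitude and social support alongside stressors such as workload and interruptions. In ERI the items do not even share a response range.

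Anxiety and depression symptoms are among the main outcomes named under Aims and objectives, and ERI is among the measures collected at all three time points. EQ-5D 5L and CSSRI supply the QALYs and direct costs for the societal analysis under Health economic evaluation. At stake are the scores of those participants for whom the rule is used. This is a rule that the document states, not a detail left to an analysis plan.

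**Working it through.** The protocol gives no figure for this rule, so there is nothing to reproduce. Three checks follow.

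**1. Share of the filled-in value that comes from other subscales.** For a subscale of k items in a questionnaire of m items with one item missing, m - 1 items are averaged and k - 1 of them belong to the right subscale. The foreign share is (m - k)/(m - 1). Item counts are the protocol's unless marked.

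| Missing item in | k | m | Foreign items / averaged items | Share |
|---|---|---|---|---|
| ERI exertion | 6 | 23 | 17/22 | 77% |
| ERI over-commitment | 6 | 23 | 17/22 | 77% |
| ERI reward | 11 | 23 | 12/22 | 55% |
| HADS anxiety or depression | 7 | 14 | 7/13 | 54% |
| PSRS, 5-item scale | 5 | 23 | 18/22 | 82% |
| PSRS, 4-item scale | 4 | 23 | 19/22 | 86% |
| OPD-SF self-awareness | 12 | 25 | 13/24 | 54% |
| KFZA, 2-item scale (assumed size) | 2 | 26 | 24/25 | 96% |
| KFZA, 3-item scale (assumed size) | 3 | 26 | 23/25 | 92% |

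The protocol does not give the KFZA scale sizes. Eleven scales of three or more items would need at least 33 items, so with 26 items some scales must have two or fewer.

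**2. Response range.** A respondent with the highest answer on every other ERI item has 17 items at 5 and 5 over-commitment items at 4. The missing over-commitment item is filled with (17 x 5 + 5 x 4)/22 = 105/22 = 4.77, above that item's maximum of 4. This needs no assumed means.

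**3. Size for an affected participant.** Item means are assumptions, because the protocol gives none.

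- *ERI exertion*, with exertion 3.0, reward 2.0, over-commitment 2.5: filled-in value (5 x 3.0 + 11 x 2.0 + 6 x 2.5)/22 = 52/22 = 2.36. The item error is 2.36 - 3.0 = -0.64, and the error in the six-item mean is -0.64/6 = -0.11.
- *Wider gap*, with exertion 4, reward 1.5, over-commitment 3: 54.5/22 = 2.48. The item error is -1.52, and the error in the six-item mean is -0.25.
- *Reversed sign*, with exertion 2.0, reward 3.0, over-commitment 2.5: 58/22 = 2.64. The item error is +0.64, and the error in the six-item mean is +0.11.
- *HADS*: the subscale sum moves by 7/13 of the gap between the two item means. For assumed gaps of 0.3 to 1.5 this is 0.16 to 0.81 points.

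**EQ-5D 5L and CSSRI.** The leaders' list is PSRS, ERI, HADS, LMX-7, BSWE, PSC-4, OPD-SF, CSSRI and EQ-5D 5L. It reaches the stated nine only with the last two, so on its literal wording the rule covers them. For EQ-5D 5L with one dimension missing, answers of 1, 1, 1 and 3 average to 6/4 = 1.5, which is not a level and has no entry in a value set. Of the 5^4 = 625 possible patterns of four answers, 157 (25%) give a whole number. The patterns are not equally likely, so 25% is not an expected frequency. For CSSRI, a mean across different kinds of resource use is neither a quantity nor a cost.

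**The case against.** The strongest answer is that the rule will hardly ever operate. The forms are digital and flag missing items, and the larger data losses that the protocol foresees (dropout, withdrawal from physiological measures) are not governed by this sentence. If, say, 5% of participants missed one ERI exertion item (an assumption), the group mean would move by about 0.05 x 0.11 = 0.005. It would move alike in both arms unless missingness or the gap between scales differed by arm. This stands, and it sets the importance of the point. It does not make the rule right, since the sentence exists for the case in which an item is missing.

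The authors may also have meant scale when they wrote questionnaire. That is possible, but the text does not say so. Likewise, talk of item scores suggests summed rating scales, so they may never have intended to average EQ-5D levels or resource-use items. A non-integer EQ-5D level would normally stop the analyst at the value set rather than bias the result unseen. That reduces this part to a needed clarification.

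Some stronger readings are tempting but unsupported:

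- *The rule spoils every questionnaire.* It does not. LMX-7, BSWE, PSC-4 and WHO-5 are single scales, and a person mean over all items is ordinary for the PSRS total.
- *The absence of a minimum number of answered items is an error.* A condensed article can leave that to the analysis plan.
- *The group comparison is biased by a known amount.* Every size above rests on assumed means, and its sign depends on which subscale is higher.

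**Conclusion.** The point holds for instruments with separately scored subscales: ERI, HADS, OPD-SF, KFZA and the PSRS subscales. As written, the rule draws about half to nearly all of the filled-in value from other constructs, and in ERI it can produce a value outside the response range. The shares for ERI, HADS, PSRS and OPD-SF and the 4.77 follow from the protocol's own item counts and formats; the KFZA shares rest on assumed scale sizes.

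For EQ-5D 5L and CSSRI the point is narrower. The wording includes them through the count of nine, and an item mean is unsuitable there. A reader might infer that the QALY and cost results will be distorted, but the documents do not show that the authors plan to apply the rule to them.

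The practical effect is probably small: about 0.11 on a six-item ERI exertion mean for an affected participant under the first set of assumed means, 0.25 under a wider gap, and close to nothing at group level if missing items are rare. It is a minor error in a stated rule, worth correcting before scoring because the correction is nearly free.

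**What to change.** Change the sentence so that a missing item takes the participant's own mean over the remaining items of the same subscale, or of the whole instrument where it has only one scale. Add that EQ-5D 5L and CSSRI are exempt from item-mean substitution, and that the affected index value or cost is treated as missing. The document names no method for missing index values or costs, so the new text should not refer to one as though it existed.

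The cost is one amended sentence and one added sentence. The downside is that a few EQ-5D or cost values become missing instead of filled in.
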